### Outcomes

2.5

Baseline data collection (T1) will occur prior to randomization within the first 3 months of the academic year (Aug. 1 – Oct. 31). Post-test data collection (T2) will occur in the last 2 months of the academic year (April 1 – May 31). Data collection for parents and implementers consists of a survey, whereas data collection for students includes a survey and biometrics assessment. Parent and implementer surveys will be administered online via REDCap (an online survey platform), whereas student surveys and biometrics (i.e., objective measures of cardiovascular disease risk) will be collected during an in-person data collection event. A summary of constructs measured is included in Table 3.

**Table 3 tab3:** Summary of constructs measured.

Construct	Implementers	Students	Parents
Implementation outcomes			
Reach	P		
Dose delivered	P		
Acceptability, appropriateness, feasibility	O		
School characteristics	O		
Perceptions of healthy school recognized campus	O		
Effectiveness outcomes			
Metabolic syndrome		P	
Cardiovascular fitness		P	
Dermal carotenoids		P	
Body mass index		P	
Psychosocial determinants of physical activity and healthy eating		O	
Physical activity	O	O	O
Frequency of foods consumed	O	O	O
Engagement in the school and community		O	O
Sociodemographic characteristics	O	O	O

P, primary; O, other.

#### Primary implementation outcomes

2.5.1

On the implementer survey, we will ask implementers which programs they chose to deliver, the classrooms that received those programs, the number of students in those classrooms, the number of sessions they delivered from those programs, and the normal session length for that program. In the student survey, we will ask the students to identify their teachers. From this data, each will be determined as the total number of students who received programs. We will also calculate the dose that each participant received (primary outcome) by multiplying the number of sessions by the session length and summing them across all programs that the students’ teachers received.

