##### School-to-school mentoring

2.4.7.2

We define the school-to-school mentoring strategy as the research team facilitating connections between schools that are implementing HSRC at the same time as one another to provide a support system and technical assistance to improve implementation outcomes (i.e., acceptability, appropriateness, feasibility) – a recommendation based on qualitative interviews and focus groups. The main components of this strategy will be: (1) an introductory email, (2) monthly meetings, (3) a private Facebook group, and (4) quarterly newsletters. Immediately following randomization, participating schools will receive an introductory email welcoming them to the school-to-school mentoring program and informing them about its components (e.g., the Facebook group, newsletters). Starting around November (1–2 months into the implementation process), the research team will host monthly virtual meetings with implementers to discuss the programs being completed and successes and barriers to program implementation. At the first meeting, implementers will be invited to join a private Facebook group, which will serve as a hub for HSRC program implementers to discuss ideas, share insights on their implementation process, and seek advice outside of the group meetings. Within the Facebook group, the research team will post prompts periodically to foster engagement with the page. Finally, schools will receive quarterly newsletters designed by the research team (up to four times during the year), which will include the following elements: (1) a previously recognized HSRC school, (2) links to helpful resources for program implementation, (3) a spotlighted HSRC program, (4) a calendar of local county health-focused events, and (5) information on AgriLife Extension and its agents.

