Finally, the HSRC initiative bundles programs within the school setting to try to improve physical activity, healthy eating, and MetS risk among students. More specifically, all students at the school participate in an 8-week school-wide walking program (i.e., Walk Across Texas) (69, 70), and smaller groups of students at the school (e.g., physical education class, after-school club) participate in additional programming. This type of bundled approach is ideal for Extension agents, as once they start delivering programs at the school, it is often easier to implement additional programs within the school setting. Additionally, schools are an important setting to improve physical activity and diet quality among youth, as students spend an average of 6.5 h there each day for over 180 days each year (9), and school-based programs are an evidence-based approach for improving obesity outcomes (5–8). Still, given that bundled approaches have had mixed effectiveness in the clinical setting (13), it is unclear if this type of bundled approach has positive effects on students’ behavioral (i.e., physical activity and healthy eating) and health outcomes within the school setting. Thus, our study will evaluate changes in health outcomes over the course of one school year. Furthermore, as the HSRC initiative also requires that parents and/or school staff participate in a physical activity and healthy eating program – recommendations aligned with school health and ecological models (15–18)– we will evaluate physical activity and nutrition outcomes in these groups to determine if HSRC has any impact beyond students. These results can help to inform further modification to the way the HSRC initiative is designed and implemented within the school setting.

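### Reach, a raw count, sits at or near enrolment where the walking program runs as described, and dose linked only through teachers misattributes club sessions

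*Protocol article*

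**What the plan says.** Table 3 of the protocol article marks two implementation constructs, reach and dose delivered, with the code for primary ("P, primary; O, other"). Section 2.5.1 is headed as the primary implementation outcomes, but in its text only dose carries that label.

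- **Reach.** The rule is "each will be determined as the total number of students who received programs". The first word is read as reach, because reach is the only other construct that the section has to define.
- **Dose.** It is obtained by "multiplying the number of sessions by the session length and summing them across all programs that the students’ teachers received". Implementers report the programs delivered, the classrooms that received them, the class sizes, the number of sessions and the usual session length. Students name their teachers. No other link from student to program is described.
- **Delivery.** Section 2.3 makes implementing the initiative a condition of school eligibility, and section 2.4.2 requires a school-wide walking challenge for recognition. The Discussion says "all students at the school participate in an 8-week school-wide walking program" and "smaller groups of students at the school (e.g., physical education class, after-school club) participate in additional programming".

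**The concern.** The two outcome rules do not fit the delivery model in the same article. A count of students with any program is filled by the one program that every school must run for everyone. That leaves little room for the strategies to show an effect through the additional programs, and a count without a denominator also carries school size into every comparison of schools with and without a strategy. Dose is meant to be what each participant received, but it follows the teacher, while additional programs may follow a club or another small group.

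Section 2.6.1 compares standardized effect estimates to decide which components to keep. Section 2.4.6 allows strategies to be removed, replaced or modified after one cohort of eight schools. An uninformative reach and a misassigned dose would feed into both decisions.

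**Working it through.** The plan gives no figure for either outcome, so there is none to reproduce. The check sets the definitions against the delivery model and adds simple arithmetic.

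**Reach**

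1. Let N be enrolment, w the share of students recorded as receiving the walking program, and a the share receiving at least one additional student program.
2. A count of students with any program lies between N × max(w, a) and N × min(1, w + a).
3. Delivery as the Discussion describes it means w = 1. Both bounds then equal N, whatever a is. Reach equals enrolment in all eight conditions of Table 2, and the proportion reached is 1.0 everywhere.
4. If w is below 1, a can matter. Suppose additional programs fall on walking and non-walking students alike (an assumption). Then reach/N = 1 − (1 − w)(1 − a), so only the fraction (1 − w) of any change in a shows up in reach. With w close to 1, that fraction is small.
5. In every case the count is multiplied by N, so differences in school size pass straight into it.

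**Dose**

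Inputs from Table 1: the walking program lasts 8 weeks; one student program has 6 sessions and another lasts 10 weeks. Assumptions: equal session lengths; one session a week for the 10-week program; walking counted either as 8 sessions (one a week) or as 40 (five a week).

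Share of a club member's dose that is missed when no named teacher is linked to the club = club sessions / (walking sessions + club sessions):

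| Walking sessions | 6-session club | 10-session club |
|---|---|---|
| 8 | 6/14 = 43% | 10/18 = 56% |
| 40 | 6/46 = 13% | 10/50 = 20% |

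Over-credit to a non-member whose named teacher is linked to the club = club sessions / walking sessions, taking walking as that student's only program:

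| Walking sessions | 6-session club | 10-session club |
|---|---|---|
| 8 | 6/8 = 75% | 10/8 = 125% |
| 40 | 6/40 = 15% | 10/40 = 25% |

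The walking program is common to all schools. The error therefore falls on the additional programs, where dose has most room to differ between schools.

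**The case against.** The strongest reply is that universal walking participation is a description of intended delivery in the Discussion, not a measurement rule. Reach is built from the classrooms that implementers report, recognition has to be earned during the year, and schools may change programs at any point. Variable delivery is what an implementation outcome is meant to detect. This stands. A reader might infer that reach cannot respond to any strategy, and the documents do not support that: a strategy that improved delivery or reporting of the walking program would raise it. Implementers are also asked for student numbers by program, so a count by program could be intended. The text does not say so, and such a count would still lack a denominator.

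On dose, students may name several teachers. Physical education sessions, and clubs led by a named teacher, can therefore be captured, and crediting all classmates alike suits the label in Table 3, dose delivered. This also stands in part: the error runs in both directions and is not simply loss. But section 2.5.1 presents the quantity as what each participant received, which is a different thing.

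Two further inferences are tempting and go too far.

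- One could assume that enrolment varies between schools with a coefficient of variation of 20–40% and derive a chance of 16–48% that a four-against-four contrast shows a spurious difference above 20%. That variation is assumed, and the calculation ignores adjustment. Section 2.6.1 names school size as an example covariate, to be included if bivariate screening identifies it. If reach equals enrolment, screening should identify it, and the adjusted outcome is then uninformative rather than misleading.
- One could infer that sessions before randomization enter the dose, because the mentoring section puts November one to two months into implementation while section 2.5 says "Baseline data collection (T1) will occur prior to randomization within the first 3 months of the academic year". But that window spans all schools, baseline is described elsewhere as pre-intervention, and no text places programming before a school's own baseline. Such sessions could not depend on assignment, so they would add noise rather than systematic bias.

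**Conclusion.** The point holds in this form. Where the walking program is delivered as described, reach is at or near enrolment, reflects school size, and barely responds to strategies that act on the additional programs. It drops below enrolment only through incomplete delivery or reporting. Its primary status rests on Table 3 and the section heading, and section 2.5.1 should agree with them.

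Dose per participant is misattributed for programs delivered to clubs or similar groups. Under the stated assumptions, a club member loses 13–56% of the dose when no named teacher is linked to the club; when one is, that teacher's non-member students are over-credited by 15–125%. These ranges illustrate single students. The effect on a strategy contrast cannot be sized, because the article does not say how much programming runs through clubs.

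The article states both rules, so this is more than detail left to a fuller plan. That the study is declared not fully powered does not help: more schools would not make either measure more valid.

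**What to change.** - Define reach as a proportion of enrolled students and report it by program, with the walking program separate from the additional student programs. The implementer survey already asks for student numbers by program for classrooms; the same question should cover clubs and other groups.
- Add one program/club participation item to the post-test student survey, and credit dose by reported group membership as well as by teacher.
- Reconcile section 2.5.1 with the Discussion's account of small-group delivery and with Table 3's dose delivered: state whether the outcome is dose delivered to a class or dose received by a student. Give reach and dose the same primary or non-primary status in Table 3 and in the text.

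The cost is one extra survey item, enrolment counts from the schools and revised scoring text. Students' reports of membership will carry some error of their own.

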**Methods:**

Using the Multiphase Optimization STrategy (MOST) framework and a cluster randomized full factorial study design, two cohorts (*n* = 8; *n* = 16 total) of public elementary schools in North and East Texas will be randomized to receive combinations of the three implementation strategies – additional resources, school-to-school mentoring, and enhanced engagement – over one academic year. We will survey program implementers (e.g., Extension agents, school staff, administrators) to determine the dose of the Healthy School Recognized Campus initiative that each student receives. We will objectively measure changes in students’ MetS risk, cardiovascular fitness measured via the Progressive Aerobic Cardiovascular Endurance Run, dermal carotenoids (an estimate of fruit and vegetable intake) measured via the Veggie Meter, and body mass index pre- and post-intervention. The individual and combined (e.g., synergistic, antagonistic) impact of strategies will be evaluated after each cohort using a general linear model framework, and strategies will be modified and prepared for testing in a future randomized controlled trial.

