#### Healthy school recognized campus (HSRC) initiative

2.4.2

For this study, all schools will agree to participate in the HSRC initiative. The HSRC initiative promotes the delivery of physical activity and healthy eating programs by bundling AgriLife Extension’s school- and research-based programs. For a school to be recognized as a HSRC, they are required to host a school-wide walking challenge to increase students’ physical activity (i.e., Walk Across Texas), at least one other AgriLife Extension program for students, and at least one AgriLife Extension program for adults (examples in Table 1; full list of programs found at https://texas4h-hsrc.com/). Including both interventions for students and their caretakers (i.e., teachers or parents) is also a benefit of this bundled approach, as interventions that address more than one level of the ecological model (e.g., intrapersonal, interpersonal, organizational) can be more effective than single level interventions (30–32). Programs are delivered by one or more Extension agents (i.e., health educators) in the county where the school is located (33, 34), and once the initiative’s requirements are complete, schools receive recognition via a banner and/or at a local school meeting (e.g., school board, school health advisory council).

**Table 1 tab1:** Examples of healthy school recognized campus’ research-based programs.

Program	Description	Research
Youth		
Walk Across Texas! (Youth) (69, 70)	8-week program designed to help youth across Texas establish the habit of regular physical activity using a fun and motivating team approach.	- Doubled the number of steps taken over the course of the program. - Increased the amount of time that students were active with their parents. - Decreased BMI percentile.
Learn Grow Eat and Go! (70, 71)	10-week program that teaches students about gardening, healthy eating, and being active.	- Increased the number of vegetables tasted, vegetable preferences, and nutrition knowledge. - Decreased BMI percentile.
Choose Health: Food, Fun and Fitness (72–74)	6-session program that encourages healthy eating and fitness through hands-on activities and experiential education.	- Improved overall dietary intake, vegetable intake, fruit intake. - Reduced soda/fast food intake. - Read nutrition labels and share about healthy eating with families more often. - More likely to try new food. -Increased frequency of doing physical activities.

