#### Statistical and power analysis

2.6.1

This is an optimization study to screen and refine components of a support strategy for the HSRC initiative in preparation for a fully powered randomized controlled trial; thus, this study is not fully powered to examine differences in implementation or effectiveness outcomes (60). To analyze outcomes, we will use univariate and bivariate statistics to determine the distribution of outcome measures and to identify relevant covariates (61). To test between-implementation strategy differences on implementation and effectiveness outcomes, students at schools with and without each implementation strategy (independent variable) will be evaluated using a generalized linear model framework. Baseline scores will be added as a covariate (when applicable), post-intervention score is the outcome, and school is a clustering variable (62). Other covariates (e.g., school size), identified in the preliminary bivariate analyses, will also be included in the model. If missing data occurs, we will mitigate potential biases by analyzing multiple imputed datasets under an intention-to-treat approach (63). Analyses will be compared to per-protocol analyses (64). Interaction effects between strategies are normally small in behavioral trials; however, we will review plots of combinations of strategies to determine if a specific combination of strategies warrants further evaluation. If so, we will add an interaction term to our model. We will calculate standardized effect estimates for each strategy (i.e., Cohen’s *d*), compare effect estimates to make decisions about which components to include in the final support strategy, and report these estimates in our results.

As the goal of this project is to refine and optimize implementation strategies for testing in a future trial, we will conduct an interim analysis following the first cohort of schools using the approach outlined above. This analysis will be repeated following the second cohort of schools. Depending on the results of the interim analysis and potential changes to the strategies that result from the interim analysis, we will conduct a pooled analysis across both cohorts, unless the implementation strategies undergo substantive modifications between cohorts, in which case we will only report the individual results from each cohort.

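### Section 2.5.1 links students to programs only through the teachers they name, so dose is over-credited when a program reaches some but not all of a named teacher's classes

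*Protocol article*

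**What the plan says.** The abstract (Methods) states that implementers will be surveyed "to determine the dose of the Healthy School Recognized Campus initiative that each student receives". The target is therefore a student-level quantity.

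Section 2.5.1 gives the rule. Implementers report which programs they delivered, "the classrooms that received those programs, the number of students in those classrooms", the number of sessions and the usual session length. On the student side the article describes one link: "In the student survey, we will ask the students to identify their teachers". Dose is then sessions times session length, "summing them across all programs that the students’ teachers received". The section labels this dose a primary outcome.

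The Discussion (section 3) says that all students take part in the 8-week walking program, while "smaller groups of students at the school (e.g., physical education class, after-school club) participate in additional programming".

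**The concern.** Delivery is recorded by classroom, but the sum runs over teachers. The rule has no step that restricts a program to the student's own class. A student who names a teacher is credited with every program that any of that teacher's classes received.

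This matters only if a named teacher has more than one class and a program reaches some of them. The article does not say how often that happens, but its own description makes it plausible. Programs beyond the walking challenge go to sub-school groups, and a physical education class is the first example given.

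Dose is a primary implementation outcome, and estimated effects are compared to decide which strategies are kept. If credited dose depends partly on whether a program ran through a shared teacher or a single-class teacher, schools that deliver the same amount can show different doses. Non-recipients recorded as recipients would also blur any relation between dose and student health outcomes.

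**Working it through.** The article gives no figure for this quantity, so there is nothing to reproduce. The check applies the stated rule algebraically and then illustrates it.

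**Inputs**
- Dose rule and teacher link: section 2.5.1.
- Number of sessions, S = 6: Table 1 (section 2.4.2) lists a "6-session program that encourages healthy eating and fitness through hands-on activities and experiential education".
- Session length, L: not given. Assumed 45 min, with 30 to 60 min as a range.
- Number of equal-sized classes per shared teacher, k: not given. Assumed 2, 4 and 6, with one class treated.
- Schools per strategy level: four in each cohort (section 2.4.6), so eight if both cohorts are pooled (section 2.6.1).

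**Step 1: one program, students of one shared teacher**
- Credited to every student who names the teacher: S × L.
- True mean over those students: S × L / k.
- Ratio of credited to true mean: k.
- Share credited with a program they did not receive: (k − 1)/k.

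With S × L = 6 × 45 = 270 min:

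| k | Credited mean (min) | True mean (min) | Share falsely credited |
|---|---|---|---|
| 1 | 270 | 270 | 0% |
| 2 | 270 | 135 | 50% |
| 4 | 270 | 67.5 | 75% |
| 6 | 270 | 45 | 83% |

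**Step 2: shift in a strategy-level mean when one school is affected**

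This assumes that schools are weighted equally, that all sampled students in the affected school name the shared teacher, and that its k classes are equally represented. The shift is (270 − 270/k) divided by the number of schools per level.

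| k | Excess in the school (min) | Four schools per level (one cohort) | Eight schools per level (pooled) |
|---|---|---|---|
| 2 | 135 | 33.8 | 16.9 |
| 4 | 202.5 | 50.6 | 25.3 |
| 6 | 225 | 56.3 | 28.1 |

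The shift is proportional to L. At 30 min per session (180 min in all) the four-school shift runs from 180 × (1/2)/4 = 22.5 min to 180 × (5/6)/4 = 37.5 min for k = 2 to 6. At 60 min (360 min) it runs from 45 to 75 min. The eight-school values are half of these.

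**Step 3: which contrasts move**

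Each of the eight conditions is assigned once per cohort (Table 2), so every school sits on one side of all three main-effect contrasts. One over-credited school moves all three by the same number of minutes, in the direction set by its condition.

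**The case against.** The strongest reply is that the article never says teachers are shared or that delivery is selective by class. The Discussion sentence is only an example, these are elementary schools, and the delivery unit in section 2.5.1 is the classroom. With one class per teacher, or with delivery to all of a teacher's classes, the rule is exact. This stands as a limit on how often the error occurs. It does not change what the rule does when it occurs. Nor is the rule a detail left to a fuller document, because the article states both the link and the sum.

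A reader might infer three stronger things that the documents do not support.

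- *That the error cannot be repaired at analysis.* The survey items are not shown. Implementers report classrooms and their headcounts, and students report grade level (section 2.5.6). Teacher, grade and classroom together may narrow the match, and the headcounts give a check on total over-crediting.
- *That the strategy comparison is systematically biased.* Schools are randomized to conditions, and nothing in the article ties delivery route to strategy. The error is mainly extra school-level variation and misclassified exposure, in a study that says "this study is not fully powered to examine differences in implementation or effectiveness outcomes".
- *That a level's dose is inflated by some stated percentage.* A percentage based on one additional program leaves out the walking program, which all students receive, and any other correctly linked program. Against total dose it would be smaller by an unknown amount.

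**Conclusion.** The point holds as a defect in how a primary outcome is constructed. The stated aim is the dose each student receives, and the stated rule credits the programs of the student's teachers. The two differ whenever a named teacher has several classes and a program reaches only some of them. For such a program with one of k equal classes treated, the mean is overstated k-fold. The error is zero at k = 1, zero when all classes receive the program, and absent for the school-wide walking program.

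The size in this trial is not computable from the documents. The illustrative shift from one affected school is 34 to 56 min with four schools per level and 17 to 28 min with eight. It rests on the assumed 45-minute sessions and k from 2 to 6. The single-cohort figure applies to the interim analysis, which informs whether strategies are removed, replaced or modified. The eight-school figure applies only if the cohorts are pooled. The expected consequence is noise and exposure misclassification. Because the remedy is cheap, the change is worth making.

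**What to change.** Record the student's class section (or period) for each teacher named, either as a field on the student survey or from the school roster. Match it to the classrooms that implementers already report for each program. Reword section 2.5.1 so that dose is summed only over programs delivered to the classes or groups the student attended.

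The cost is one extra survey field or a roster request, some matching work and one revised sentence. The design, sample size and strategies stay as they are.
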